# Prevention of diabetes in overweight/obese children through a family based intervention program including supervised exercise (PREDIKID project): study protocol for a randomized controlled trial

**DOI:** 10.1186/s13063-017-2117-y

**Published:** 2017-08-10

**Keywords:** Type-2 diabetes, Children, Exercise, Family based lifestyle intervention program, miRNA, Ectopic fat

## Abstract

**Background:**

The global pandemic of obesity has led to an increased risk for prediabetes and type-2 diabetes (T2D). The aims of the current project are: (1) to evaluate the effect of a 22-week family based intervention program, including supervised exercise, on insulin resistance syndrome (IRS) risk in children with a high risk of developing T2D and (2) to identify the profile of microRNA in circulating exosomes and in peripheral blood mononuclear cells in children with a high risk of developing T2D and its response to a multidisciplinary intervention program including exercise.

**Methods:**

A total of 84 children, aged 8–12 years, with a high risk of T2D will be included and randomly assigned to control (*N* = 42) or intervention (*N* = 42) groups. The control group will receive a family based lifestyle education and psycho-educational program (2 days/month), while the intervention group will attend the same lifestyle education and psycho-educational program plus the exercise program (3 days/week, 90 min per session including warm-up, moderate to vigorous aerobic activities, and strength exercises). The following measurements will be evaluated at baseline prior to randomization and after the intervention: fasting insulin, glucose and hemoglobin A1c; body composition (dual-energy X-ray absorptiometry); ectopic fat (magnetic resonance imaging); microRNA expression in circulating exosomes and in peripheral blood mononuclear cells (MiSeq; Illumina); cardiorespiratory fitness (cardiopulmonary exercise testing); dietary habits and physical activity (accelerometry).

**Discussion:**

Prevention and identification of children with a high risk of developing T2D could help to improve their cardiovascular health and to reduce the comorbidities associated with obesity.

**Trial registration:**

ClinicalTrials.gov, ID: NCT03027726. Registered on 16 January 2017.

**Electronic supplementary material:**

The online version of this article (doi:10.1186/s13063-017-2117-y) contains supplementary material, which is available to authorized users.

## Background

Type-2 diabetes (T2D) is an important cause of premature death and disability as well as a costly disease affecting more than 415 million people worldwide [1]. This chronic disease is an important risk factor for developing accelerated cardiovascular disease and is the leading cause of microvascular complications such as end-stage renal disease, blindness and limb amputations. T2D was traditionally viewed as an adult-onset disease; however, over the last two decades scientific literature shows a global and dramatic increase in the incidence of T2D in youth [2], secondary to the coincident pandemic of childhood obesity [3]. The life-time risk of developing microvascular and macrovascular complications and mortality in early adulthood can be expected to be higher when the onset is already in children/adolescents rather than in adults with T2D or insulin resistance syndrome (IRS) due to the longer duration of the disease and greater duration of glycemic exposure [2, 4, 5].

As a consequence of the high rates of obesity and diabetes risk, health and scientific organizations demand urgent early preventive actions for increasing life expectancy and quality of life of overweight/obese children at a high risk of T2D [1, 6, 7]. T2D in youth is largely preventable through lifestyle intervention programs based on increasing physical activity levels, improving dietary habits and promoting a healthy body weight [8]. Likewise, overweight and obesity are the strongest risk factors for insulin resistance and T2D [9, 10]. However, long-term success rates of lifestyle intervention programs focused on T2D prevention or treatment in children are usually less than 10% [11]. The etiology of this apparent inefficiency of lifestyle intervention programs is multifactorial: lack of multidisciplinary approaches, high rates of depression or anxiety which affect the adherence to the program, insufficient involvement of the parents, etc. [12–14]. Therefore, there is a need for studies examining the effect of family based multidisciplinary intervention programs on metabolic abnormalities closely associated to T2D risk in order to give appropriate treatment/prevention options for prediabetes and T2D in overweight/obese children.

In adults, lifestyle intervention programs based on diet and physical activity level modifications have proven to be effective in decreasing the rate of the progression from glucose intolerance or prediabetes to T2D [6]. However, body mass loss achieved reducing energy intake is the cornerstone to the treatment in adults [6]. In children, energy restriction programs may compromise healthy growth and development, and increase the risk of disordered eating behaviors.

There is substantial evidence indicating that lifestyle behaviors associated to obesity and T2D are established in childhood and are difficult to modify into adulthood [15]. The adoption of healthy dietary habits is essential in the prevention of the onset of T2D in children at high risk of T2D. Consumption of sugar-sweetened beverages [16], energy-dense diets [17], reduced consumption of fiber, fruits and vegetables [18, 19], breakfast and meal skipping [20] or eating frequency [21] have been consistently associated with obesity and T2D risk. In addition, previous studies have shown the association of low physical activity levels and sedentary behaviors with insulin resistance in children [22]. Moreover, short sleep duration and poor sleep quality have been proposed as predictors of obesity and T2D onset in children and adults [23, 24].

Family based lifestyle modification interventions (i.e., targeting both the child and parent) seem to be the most efficacious treatment format for childhood obesity [25]. In addition, psychological and emotional factors are important determinants of lifestyle modifications [26] and depressive symptoms and psychological stress have negative effects on dietary behaviors and physical activity levels [27]. Moreover, overweight/obese children have an impaired psychological wellbeing compared to their non-overweight peers [28]. In this context, multicomponent lifestyle management aiming to promote healthy dietary and sleep habits, increase physical activity levels and reduce sedentary behaviors may contribute to the prevention of T2D in the short and the long term [29, 30].

Exercise is a critical component for T2D prevention and management. Likewise, regular physical activity improves insulin sensitivity in diabetic or prediabetic children [31]. Previous studies have shown that exercise training reduces insulin resistance in overweight/obese youth, even without body mass loss [32]. Interestingly, Davis et al. reported that the benefit of aerobic training on insulin resistance was dose-dependent in overweight children regardless of sex and race [33]. However, although exercise is recommended for overweight/obese children, optimal exercise prescription describing type (aerobic training, resistance training or combined training) and intensity (moderate or vigorous) of exercise needed to reduce T2D risk in children is unclear.

Obesity, insulin resistance and T2D are caused by a combination of genetic, epigenetic and environmental factors such as diet and exercise. During the last few years, a growing number of studies demonstrate that small, non-coding, ribonucleic acid (RNA) molecules that function as regulators of gene expression, microRNAs (miRNAs), may be involved in the pathogenesis of obesity, diabetes and related metabolic disorders [34, 35]. Several studies observed that miRNAs play a significant role in insulin production and secretion, pancreatic islet development and β-cell differentiation, and that they are implicated in several aspects of glucose homeostasis and lipid metabolism associated with the pathogenesis and progress of T2D and obesity [36–38]. The stability and presence of miRNAs in a variety of readily accessible cell types including body fluids, as well as their often tissue- and disease-specific expression, and the possibility to measure them with high sensitivity and specificity, render them a potential source of clinical biomarkers of T2D risk [39]. Moreover, miRNAs reflect individual biological adaptations to physiological changes or environmental exposures such as diet or exercise. Likewise, measurement of miRNAs presents an opportunity to evaluate biological changes associated with lifestyle interventions for the reduction of metabolic disorders associated with T2D risk such as insulin resistance, ectopic fat accumulation, inflammation, etc. The majority of the studies aiming to identify miRNAs as biomarkers of obesity and T2D have been conducted in small samples of adults. Previous reports observed changes in circulating miRNA profile after metformin therapy [38] or exercise in prediabetic adults [40]. In obese children, several miRNAs have been proposed as biomarkers of endothelial dysfunction and dyslipidemia [41]. As far as we are aware, there are no previous studies identifying the profile of miRNAs in children at a high risk of T2D and its response to a family based multidisciplinary intervention program including exercise.

Therefore, the primary aims of the PREDIKID (Prevention of Diabetes in Kids) study are: (1) to evaluate the effect of a 22-week, family based, multidisciplinary intervention program including exercise on IRS in children with a high risk of developing T2D and (2) to identify the profile of microRNA in circulating exosomes and in peripheral blood mononuclear cells in children with a high risk of developing T2D and its response to a family based multidisciplinary intervention program including exercise.

## Methods

### Design

The PREvention of DIabetes in KIDs (PREDIKID) study is a randomized clinical trial (RCT) (ClinicalTrials.gov, ID: NCT03027726) (see Additional file 1 and Fig. 1 for the associated Standard Protocol Items: Recommendations for Interventional Trials (SPIRIT) Checklist and Figure, respectively). Children will be randomly allocated to the control group or the exercise group and will be followed for 22 weeks. All the families included in the study will participate in a lifestyle education and psycho-educational program conducted by a multidisciplinary team of health care professionals (physicians, nutritionists and dieticians, psychologists and exercise specialist) and scientists. As both groups will receive the same lifestyle education and psycho-education program, differences in changes in outcome variables will be due to the additional effect of the exercise intervention. This study was reviewed and approved by the Ethics Committee of Clinical Investigation of Euskadi. All parents or legal guardians will sign an informed written consent and all the children will give their assent before being enrolled in the study. The informed consent will be obtained by the pediatricians participating in the recruitment.

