#### Participants and selection criteria

Participants will be recruited by pediatricians from the Pediatric Endocrinology Unit of the University Hospital of Txagorritxu and from primary care clinics (Vitoria-Gasteiz, Spain). Children aged between 8 and 12 years, meeting the international criteria for classification of T2D risk [1, 42], and having at least one parent or caregiver willing to participate in the program sessions, will be included (Table 1).

**Table 1 Tab1:** Eligibility criteria for the PREvention of DIabetes in KIDs (PREDIKID) study

Inclusion criteria
Aged 8–12 years
Criteria for the classification of risk of T2D [1]^a^
1. Obesity status according to the World Obesity Federation [24] 2. Overweight and the presence of at least one of the following metabolic abnormalities: 2.1. Family history of T2D in first- or second-degree relative; Signs of insulin resistance or conditions associated with insulin resistance (acanthosis nigricans, HOMA > 2.5, glucose between 100 and 125 mg/dL; Hypertension (systolic blood pressure ≥ 130 mmHg and/or diastolic blood pressure ≥ 85 mmHg); Dyslipidemia (HDL < 40 mg/dL, TG > 150 mg/dL); 2.2. Ethnic minority with higher risk
To have at least one parent or caregiver willing to participate in the program sessions
Exclusion criteria
Not available for assessment and intervention sessions
Medical conditions or medications that would affect study results or limit physical exercise

*PREDIKID* PREvention of DIabetes in Kids. ^a^According to the International Diabetes Federation [1]. *T2D* type-2 diabetes; *TG* triglycerides; *HDL* high-density lipoprotein; *HOMA* homeostatic model assessment

A pre-screening appointment will be scheduled with the investigation team to assess eligibility, family needs and commitment. Parents will provide the child’s and family health history and detailed contact information. After completion of the informed consent process, children will undergo anthropometric screening (height, body mass and waist circumference), complete physical examination and blood sampling, and will be selected for inclusion in the study if they meet the inclusion criteria (Table 1). Every child meeting the inclusion criteria will go through maximal exercise testing guarantee. Children with any medical condition that could affect the results of the study or that limits physical activity will be excluded.

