#### Randomization

Eligible participants will be randomly assigned after completing the baseline measurements to either the control group or the or exercise group (Fig. 2). Randomization of the participants into the control or exercise group will be done using Statistical Package for Social Sciences (IBM SPSS Statistics for Windows, version 21, Armonk, NY, USA) by an independent researcher. Assessment staff will be blinded to participant randomization assignment. Participants and their parents or guardians will be explicitly informed of the group to which they will be assigned, as well as of the study hypotheses. As exercise is potentially beneficial for the health of the children recruited in this trial, the waiting list control group strategy will be used, which means that the control group will receive the same exercise program when the post-intervention evaluations are finished.

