#### Family based healthy lifestyle education and psycho-educational intervention

Families in the control and the exercise groups will attend both the healthy lifestyle education and psycho-education program once every 2 weeks (11 sessions over 22 weeks) for 90 min (45 min in the healthy lifestyle education program and 45 min in the psycho-educational intervention). The design of the programs has been published elsewhere [45]. Briefly, the sessions of the healthy lifestyle education and psycho-educational interventions will be developed simultaneously and delivered to both parents (or caregivers) and children, separately.

The family based healthy lifestyle education program will be conducted by experienced nutritionists. The aim of the program will be in promoting changes in lifestyle behaviors strongly associated to obesity and T2D risk: promoting healthy dietary habits (reducing the intake of sugar, sugar-sweetened beverages and energy-dense foods, enhancing the daily consumption of fruits and vegetables, promoting breakfast and eating five meals/day), increasing regular physical activity levels, reducing time spent in sedentary behaviors and promoting sleep hygiene and adequate sleep duration.

The aims of the psycho-educational program will be to provide parental skills to optimize the family environment in order to make positive changes in their lifestyles and to learn assertive communication skills. The program will also provide skills to children for managing the emotions and feelings that they are experiencing and to improve their self-esteem and psychological wellbeing.

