#### Exercise training intervention

The exercise group will do exercise 3 days/week, 90 min per session, over a 22-week period. The program will be open to the families 5 days per week to choose a total of 3 days/week. Sessions will be designed and supervised by exercise specialists. The design of the exercise program has been published elsewhere [45]. Briefly, the program consists of cardiovascular endurance (60 min) and muscle strength exercises (10 min). The sessions also include 10 min of warm-up period, 5 min for giving instructions and 5 min of cool-down period at the end, consisting mainly of stretching exercises. Moderate to vigorous intensity aerobic workout is the main part of the exercise session (60 min) and consists of games, circuits and start-and-stop activities. The emphasis of the program is on intensity doing special emphasis on high intensity activities (above 75% of maximal heart rate (HRmax) obtained from either the cardiopulmonary exercise test in the laboratory or the 20-m shuttle run test) and enjoyment. Participants will wear a heart rate monitor (Polar RS300X) during the exercise sessions to ensure achievement of the target heart rate zone. Heart rate monitors will be programmed according to individual percentage of HRmax as follows: (1) very light intensity: from 50 to 57% of HRmax, (2) light intensity: from >57 to 64% of HRmax, (3) moderate intensity, from >64 to 76% HRmax, (4) high intensity or vigorous: from >76 to 96% HRmax and (5) maximal intensity: > 96% of HRmax.

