### Data analyses plan

All outcome variables will be checked for normality and results will be expressed as mean and standard deviation (SD) or median and ranges. Multiple regression analyses will be performed to examine the potential independent predictors of T2D risk. At baseline, differences in continuous variables between groups (control group vs. exercise group) will be analyzed by Student’s *t* test or the Mann-Whitney *U* test, as appropriate. Differences in categorical variables at baseline between the two groups will be explored by chi-squared tests. Repeated-measured analysis of variance will be used to assess the effect of exercise (time (pre-post 22-weeks’ intervention) × group interactions) on the primary (insulin resistance) and secondary study (adiposity, ectopic fat, cardiorespiratory fitness, cardiovascular disease risk factors, inflammation markers, etc.) outcomes and the intention-to-treat principle will be applied. For sensitivity analyses, we will analyze the effect of the adherence to the program on the results of the intervention.

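### Children are randomised singly into a family-delivered programme, so siblings could be split between arms and dilute the HOMA contrast modestly; separately, shared exercise sessions may make its standard error too small

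*Protocol article*

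**What the plan says.** Allocation is per child. The Design section states: "Children will be randomly allocated to the control group or the exercise group and will be followed for 22 weeks". The Randomization section repeats this: "Eligible participants will be randomly assigned after completing the baseline measurements". Neither section mentions siblings or households.

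Delivery is described by family. The section on the education and psycho-educational intervention says: "Families in the control and the exercise groups will attend both the healthy lifestyle education and psycho-education program once every 2 weeks". Its sessions are "delivered to both parents (or caregivers) and children, separately". On exercise, which only the exercise arm receives during the 22 weeks: "The program will be open to the families 5 days per week to choose a total of 3 days/week". The main part of each session "consists of games, circuits and start-and-stop activities" under specialist supervision.

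Eligibility (Table 1) is set per child aged 8-12, with no limit of one child per family. One of its risk criteria, "Family history of T2D in first- or second-degree relative", is common to full siblings, and so is ethnic minority status.

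The sample size (34 evaluable per group, 42 recruited) is an ordinary two-group calculation. The Data analyses plan says: "Repeated-measured analysis of variance will be used to assess the effect of exercise". It names a time-by-group interaction and no family or session term. Attendance at every programme is to be recorded (Participant retention and adherence).

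**The concern.** Two separate mechanisms are at issue.

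**Split households.** The rule as written can put one sibling in each arm. The family then has no single allocation, although the delivery sections speak of families as belonging to one. The Design section attributes any between-arm difference in change to exercise alone. That attribution is weakened for a control child whose sibling is training, and the Randomization section adds that families are told both their group and the study hypotheses. Spillover would pull the arms together and bias the HOMA effect towards zero. It cannot be undone after allocation.

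**Shared sessions.** Children who train together with the same staff may have correlated changes in HOMA. Correlation present in the exercise arm and ignored in the model makes the standard error too small. The true false-positive rate then exceeds 0.05 and the planned sample gives less than 80% power.

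**Working it through.** **Step 1. The plan's own figure.** Inputs from Sample size calculation: d = 0.7, alpha 0.05, power 80%. The two-sided two-sample t test (noncentral t) gives power 0.7997 with 33 per arm and 0.812 with 34. So 34 is the smallest number reaching 80%, and the stated figure reproduces. It contains no design effect.

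**Step 2. Dilution from split siblings.** The number of pairs and the degree of spillover are not in the article; both are assumed. With 42 per arm, the chance that a pair is split is 42/83 = 0.506. The expected number of split pairs is s = pairs × 0.506, and each contributes one affected control. If such a control receives a fraction c of the exercise effect, the diluted effect is d = 0.7 × (1 − c·s/42).

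| Pairs (assumed) | s | c (assumed) | d | Power at 34 per arm |
|---|---|---|---|---|
| 0 | 0 | – | 0.700 | 81% |
| 4 | 2.02 | 0.5 | 0.683 | 79% |
| 4 | 2.02 | 1.0 | 0.666 | 77% |
| 8 | 4.05 | 0.5 | 0.666 | 77% |
| 8 | 4.05 | 1.0 | 0.633 | 73% |

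**Step 3. Do siblings affect the standard error?** Simulation of the unadjusted comparison with 34 per arm, an assumed sibling correlation of 0.4, and 4 or 8 pairs (15,000 runs each):

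| How siblings are allocated | True SE / model SE | Type I error |
|---|---|---|
| Individually, as the article states | 1.00 to 1.01 | 4.9% to 5.3% |
| Every pair split | 0.97 to 0.95 | 4.4% to 4.0% |
| Kept together, family ignored | 1.02 to 1.06 | 5.6% to 6.5% |

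Positive correlation across arms reduces the variance of a difference, so splitting is slightly conservative. Keeping siblings together needs a household term in the model.

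**Step 4. Session clustering in the exercise arm only.** As a first approximation take fixed groups of size m. The design effect in that arm is DEFF = 1 + (m − 1) × ICC, and the SE ratio for the contrast is the square root of (1 + DEFF)/2. For m = 10 and ICC 0.05, DEFF = 1.45 and the ratio is √1.225 = 1.11. Power by the normal approximation (82% without clustering) is shown for groups of 10; both m and the ICC are assumed.

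| ICC (assumed) | SE ratio | Power |
|---|---|---|
| 0.01 | 1.02 | 81% |
| 0.05 | 1.11 | 74% |
| 0.10 | 1.20 | 67% |

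Simulation with the exercise arm in 3 to 6 fixed groups gives type I error of about 5.2-5.6% at ICC 0.01, 6.4-7.7% at 0.05 and 7.7-11.5% at 0.10.

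**Step 5. The attendance pattern actually described.** Families choose three of five days, which gives ten possible combinations, any two sharing at least one day. There are no fixed groups. Simulating five day effects with random three-day attendance gives type I error from about 5% to 17% over ICC 0.01 to 0.10. The higher figures arise when each child's shared variance is held equal to the ICC, the lower ones when the day effects are scaled down.

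**The case against.** The strongest reply is that the sibling problem is hypothetical. The article nowhere says that siblings will enrol, it condenses a longer protocol that may hold a sibling rule, and speaking of families in an arm is natural shorthand for the families of the children in it. The spillover route is also weak. No section says that parents exercise, the parent-directed component is identical in both arms, and what differs is supervised training three times a week. Nothing in the article supports a control sibling receiving 50% to 100% of that effect. All this stands, and it is why the dilution is put as modest and conditional. It does not remove the point: the stated rule permits a split household, and the preventive change is nearly free.

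A reader might infer that split siblings make the confidence interval too narrow. Step 3 shows the opposite direction. A reader might also infer that the interval is certainly too narrow because of shared sessions. The article gives no ICC, session size or fixed groups, and at ICC 0.01 with fixed groups the effect is negligible.

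It can further be said that free choice of days dilutes the clustering. Step 5 does not bear this out in general: mixed attendance changes which model suits the design but does not by itself remove the shared variance. Finally, treating children as independent is common in small individually randomised trials, and a session term is often left to an analysis plan that is not shown. That is a fair reason to ask for a sensitivity analysis and leave the primary model otherwise as planned.

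**Conclusion.** The point holds in a limited form. Allocation by child, delivery by family and no one-child-per-family limit together allow siblings to be split. The consequence would be dilution of the HOMA contrast: about 2 to 4 points of power with 4 sibling pairs and up to about 8 points with 8, under spillover fractions that are assumed and probably generous.

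Session clustering is a real but conditional threat to the standard error. Depending on the assumed ICC (0.01 to 0.10) and how sharing is modelled, the type I error of the planned test could lie anywhere from nominal to about 17%. The article cannot narrow that range.

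The allocation rule is the firmer part, because it does not depend on any ICC and must be settled before children are allocated. The clustering part is secondary.

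**What to change.** 1. In Design and Randomization, make the household the unit of allocation, with one draw per household so that siblings always share an arm. If any siblings enrol, add a household term to the model in the Data analyses plan, since keeping siblings together while ignoring the family inflates type I error slightly (Step 3).

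2. In the Data analyses plan, add a sensitivity analysis of the HOMA effect that allows for exercise-session clustering. Use the attendance already being recorded, in a multiple-membership or attendance-pattern term for the exercise arm. A nested random effect for a fixed training group would not match the open-day scheme.

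**Cost.** A sentence or two in each place, with no extra children or visits. Arm sizes may differ from 42 by one or two. The sensitivity interval may be materially wider and imprecise, because few sessions or days carry the information. As a guide from the simpler fixed-group case with Satterthwaite degrees of freedom at ICC 0.05, it would be about 42% wider with 3 groups, 24% with 4 and 13% with 6. With 3 groups it would be about 17% wider even at ICC 0. That loss is why this analysis should support the primary one and not replace it.
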